### Withdrawal and dropout

2.9

If subjects do not meet the inclusion or exclusion criteria or if they withdraw their consent, they will be excluded from the study. The researcher will report the reason for the interruption and if each participant completed the study.

### Safety

2.10

Occurrence of side effects will be assessed at each visit. Subjects will be monitored for undesirable or unintended symptoms, signs, and diseases. The number and ratio of subjects who have experienced adverse event will be counted and calculated.

### Ethics

2.11

This study design is based on the Helsinki Declaration and the Korean Clinical Practice Guidelines. This study has been approved by the Korean Institutional Review Board of DUCKMH (number DJUMC-2019-BM-10-1). This study protocol is registered with the Korean National Clinical Research Information Service (CRIS-KCT0004272). In case of serious adverse events, subjects will be required to withdraw. They will be reported to the Institutional Review Board of the hospital. Any participant in this study may withdraw consent or voluntarily cease to participate at any time for any reason.

## Discussion

3

The immune system is an organization of cells and molecules with specialized roles in defending against infection. Innate responses occur regardless of how many times the infectious agent is encountered, whereas adaptive responses continually improve with repeated exposure to a given infection. The innate responses use phagocytic cells (i.e., neutrophils, monocytes, and macrophages) that release inflammatory mediators (i.e., basophils, mast cells, and eosinophils), and NK cells.^[14]^

NK cells are effector lymphocytes of innate immunity endowed with constitutive cytolytic functions. Moreover, NK cells also show efficacy against assaults like viral infections and tumor development.^[15]^ It is important to include assays of NK cell markers, peripheral WBCs, TNF-α, IFN-γ, IL-1β, IL-2, IL-6, IL-12 as immunological biomarkers, as well as IgG1, IgG2, and IgM as allergic biomarkers.

In previous studies, PL has been shown to have anticancer effects through stimulating immune function. This study is the first to be conducted that will determine the appropriate dosage and duration of PL administration in human subjects. Although our sample size is small, and resultant biases may occur, this study may provide valuable insights into the mechanisms underlying the immune-stimulating effects of PL and will lay the foundation for further studies on the effect of PL on symptoms in patients with immune problems.

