## Introduction

1

As the prevalence of chronic diseases is increasing, treatments for enhancing immunity are receiving more attention.^[1]^ Immune-related treatments can involve 2 approaches: enhancing an individual's immunity, which aims to strengthen the body's biological defense mechanisms and alleviating hypersensitivity, which aims to control allergic reactions. It is known that along with aging, immunological biomarkers deteriorates, it can increase the frequency and severity of inflammation and the incidence of self-immune diseases and cancer.^[2]^

As nutrition plays an important role in maintaining the immune functions of the human body, increasing attention has been paid to health functional foods, as they are known to have effects on improving immune function.^[3]^ One health functional food, *Phellitus linteus* (PL), belongs to the fungal family *Hymenochaetaceae* and grows on mulberry trees.^[4]^

In previous studies, the anticancer activity of PL has been examined. In 1968, Ikekawa et al^[5]^ reported that hot water extracts from *Polyporaceae* mushrooms inhibit the growth of sarcoma-180, and among those, PL extract was highly effective. Oh^[6]^ reported that proteoglycan separated from PL increases the production of interleukin (IL)-12 (IL-12) and interferon-γ (IFN-γ). Kong et al^[7]^ also reported that water extract of PL may be associated with augmentation of natural killer (NK) cell function in cancerated hosts. PL is known to suppress tumor growth, invasion, and angiogenesis^[8]^ and PL is also known to cause tumor regression by inducing apoptosis.^[9]^ Several other studies have reported that PL stimulates humoral and cell-mediated immunity by stimulating T-lymphocytes, NK cells, macrophages, and B-lymphocytes.^[10–12]^

This study protocol was designed to verify the safety and efficacy of PL on the immune system using a single-center, randomized, placebo-controlled, and double-blinded clinical pilot trial.

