### Sample size calculation

2.3

We have demonstrated in both in vitro and in vivo experiments that PL has immunological effects. To determine the minimum effective concentration, PL was administered at various concentrations, and 200 and 400 mg/kg of PL was administered to mice for 7 days. Based on the United States Food and Drug Administration (FDA)'s guidelines for calculating the effective dose in humans, we used body surface area to translate the effective dose in animal studies to human studies. Based on these calculations, the effective dose in the human body was set at 960 and 1920 mg. For ease of production and intake, the dose was set at 1000 and 2000 mg. According to Whitehead et al^[13]^ in preliminary parallel-designed studies when effect size is considered medium, the empirically optimal sample size is 10 persons per group, due to considerations of feasibility, estimated average, and dispersion accuracy. Therefore, we designed a pilot study with 10 subjects in each group.

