### Statistical analysis

2.8

Statistical analysis will be performed using the principle of full analysis set. For intention-to-treat (ITT) analysis, missing values will be analyzed by last observation carried forward (LOCF). The baseline values before treatment and the changes in NK cell activity at 4 weeks and after treatment will be measured for the 2 experimental groups and the control group. If the data follow a normal distribution, an independent *t* test will be performed to test the differences between 2 groups of continuous variables. If not, Mann–Whitney *U* test will be performed. Paired *t* tests will be performed to test the differences between groups if the data follow a normal distribution. If not, Wilcoxon signed-rank test will be performed. The test of normality for continuous variables will be analyzed using the Shapiro-Wilk test. The confidence level will be set at 5%. All statistical analyses will be performed using SPSS Statistics for Windows Version 20.0 (IBM Corp., Armonk, NY).

Drinking alcohol, which can affect the weekly evaluation, is considered a management variable, and if there is a difference between groups, an analysis of covariance (ANCOVA) will be performed. Descriptive statistics, such as number of subjects, mean, standard deviation, minimum, median, and maximum will be presented for baseline, at each visit, and at final evaluation. Change from baseline to final evaluation will be reported for continuous data, clinical laboratory tests, and vital signs. For categorical data, a division table will be provided. If necessary, 95% confidence intervals will be calculated. No intermediate analysis will be performed.

Demographic variables measured during the screening period will be summarized for each treatment group. Assays for comparison of drug administration groups will be performed. For this purpose, the continuous data will be tested using the *t* test or Wilcoxon rank-sum test. Categorical data will be analyzed using a chi-square test or Fisher exact test.

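### A 10-per-arm pilot in which every arm takes product for 8 weeks cannot determine dosage or duration or verify efficacy; the aim should be restated as preliminary estimation, with between-group intervals made mandatory

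*Protocol article*

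**What the plan says.** **Aims.** The Introduction says: "This study protocol was designed to verify the safety and efficacy of PL on the immune system". The same sentence ends by calling the study a pilot. The Discussion goes further: "This study is the first to be conducted that will determine the appropriate dosage and duration of PL administration in human subjects". The sentence after it admits that the sample is small and that biases may follow, and presents the study as groundwork for later research.

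**Sample size.** Section 2.3 relies on a cited rule for preliminary parallel-group studies with a medium effect, which it does not quantify. It gives the rule as: "the empirically optimal sample size is 10 persons per group, due to considerations of feasibility, estimated average, and dispersion accuracy". It concludes: "Therefore, we designed a pilot study with 10 subjects in each group". No significance level, power, standard deviation or target difference enters.

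**Regimens.** Sections 2.1 and 2.5 give every arm (1000 mg, 2000 mg, placebo) the same 8-week course, with evaluations at weeks 4 and 8.

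**Reporting.** Section 2.8 sets out two-group tests for continuous outcomes. It commits to means, standard deviations and other descriptives at each visit, and to change from baseline. On intervals it says: "If necessary, 95% confidence intervals will be calculated". The safety part of section 2.8 separately mentions 95% intervals within groups for laboratory results and biomarkers. The Abstract names a repeated measures analysis for primary efficacy.

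**The concern.** Section 2.3 justifies a study that yields first estimates of a mean and a spread. The Introduction and Discussion promise conclusions of another kind: that efficacy will be verified, and that dosage and duration will be settled. Readers who plan the next trial may take those sentences at face value.

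The promise on duration requires a comparison that the design does not contain. The promises on efficacy and dosage require precision that 10 per arm does not give. The output that would show a reader how little is settled, the interval around each between-group difference, is the one that section 2.8 leaves to discretion. Without it, a result above 5% gives no indication of which effects remain compatible with the data.

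**Working it through.** **1. The plan's own figure.** Three arms of 10 give 30, which agrees with section 2.1. The 10 per arm is a rule of thumb and cannot be reproduced from a formula. As a cross-check, a two-sided 5% comparison of two means with 80% power at a difference of 0.5 SD needs 63 per arm (normal approximation) or 64 (t test). So 10 is not a sample size for a hypothesis test, and section 2.3 does not present it as one.

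**2. Duration.** No arithmetic is needed.

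| Claim (Discussion) | Design (sections 2.1 and 2.5) |
|---|---|
| Duration will be determined | One course length, 8 weeks, in all arms |
| | Nobody is assigned to stop at week 4 or to continue past week 8 |

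Readings at weeks 4 and 8 give a time course under one regimen. They do not compare course lengths.

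**3. Precision for any pair of arms.** Inputs: n = 10 per arm (section 2.3), all analysed; common SD of the outcome as the unit; 95% level.

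- Half-width = t(0.975; 18 df) × √(1/10 + 1/10) = 2.101 × 0.447 = **0.94 SD**.
- With the variance pooled over three arms (27 df): 2.052 × 0.447 = 0.92 SD.

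The same width applies to each dose against placebo and to 1000 mg against 2000 mg.

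**4. Power, for illustration only.** The protocol gives no number for a medium effect. Assume d = 0.5, with a range of 0.3 to 0.8. The test is the two-sample t test named in section 2.8, at 5%. Sidedness is not stated; two-sided is assumed. The noncentrality is d × √(10/2) = 2.236 d, on 18 df.

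| d | Noncentrality | Power |
|---|---|---|
| 0.3 | 0.67 | 9.7% |
| 0.5 | 1.12 | 18.5% |
| 0.8 | 1.79 | 39.5% |
| 1.32 | 2.96 | 80% |

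Variants at d = 0.5:

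- one-sided test: 28.5%
- three-arm ANOVA at f = 0.25: 19.5%
- ANCOVA on baseline, assumed baseline correlation 0.3 to 0.7: 19.9% to 31.7%
- Bonferroni for two comparisons with placebo: 11.6%

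None of these comes near a conventional level.

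**5. What the pilot does deliver.** With 27 df, the 95% limits for the pooled SD are √(27/χ²) times the estimate, that is 0.79 to 1.36 times it (−21% to +36%). This is usable for planning a later trial, and it is the kind of output that section 2.3 describes.

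**The case against.** The strongest case on the other side is that this is an openly declared pilot. The Introduction's sentence contains that word, section 2.3 repeats it, and the Discussion concedes the small sample directly after the claim. Pilots are small by design, and 10 per arm is not an error. All of this stands. The hedge, however, speaks of sample size and bias. It does not withdraw the claim to determine dosage, and it does not touch duration, where a caveat cannot supply a missing comparison.

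A second objection is that a dose can be carried forward without a significant difference, by taking the arm with the higher mean. With 10 per arm, the truly better arm would rank first with probability Φ(d/√0.2): 67% if the doses differ by 0.2 SD, 87% at 0.5 SD. That is some information, but the protocol states no such selection rule, and ranking two arms is weaker than determining a dosage.

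Three stronger readings are tempting and are not supported:

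- *The trial misses its own power.* Section 2.3 claims no power and does not define medium; 0.5 SD is an assumption made here.
- *The quantities that the pilot was sized for are optional.* Section 2.8 commits to means, SDs and change from baseline. Only the between-group efficacy intervals depend on perceived need.
- *The plan will read a non-significant result as no effect.* No passage says so. Nor does section 2.8 rank tests above descriptives.

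**Conclusion.** The point holds as a mismatch between the stated aim and the design.

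- **Duration:** it holds without any assumption, because one course length is used throughout.
- **Efficacy and dosage:** it rests on a half-width of about 0.94 SD for every pairwise difference, with 10 analysed per arm and an unadjusted comparison. Baseline adjustment or a repeated measures analysis could narrow this; missing data would widen it. The power figures (about 10% to 40% for d = 0.3 to 0.8) are illustrative and contradict no figure in the protocol.

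A reader might infer that the trial should be enlarged. The documents do not support that: the size suits the purpose that section 2.3 gives. What should change is the claim and the reporting of intervals. The correction is worth making because it is cheap and governs how the results will be read.

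**What to change.** 1. **Introduction and Discussion.** Replace the wording on verifying efficacy and on determining dosage and duration with: *estimate preliminary effects of two doses given for 8 weeks, to plan a later trial*.
2. **Section 2.8.** Replace the conditional sentence on intervals with a commitment: *the difference of each dose from placebo in change in NK cell activity will be reported with its 95% confidence interval, and p > 0.05 will be treated as inconclusive*. This should sit within whatever primary analysis is kept. The Abstract names a repeated measures analysis, and the change does not require week 8 alone to become primary.
3. **Section 2.3, optional.** State the expected half-width of about 0.9 SD for a difference between two arms. A power figure is not needed, since the trial was not sized on power.

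**Cost.** The stated aim becomes less ambitious, and two between-group intervals become mandatory output. Sample size, doses and schedule do not change.
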